#### Plans to promote participant retention and complete follow-up {18b}

Participant retention is promoted by regular contact with the participant. A reminder of an upcoming visit will be sent by e-mail or via a phone call, depending on the participant’s preference. Furthermore, study visits will, whenever possible, be scheduled on the same day of a regular clinic visit to minimize the number of extra visits. If a participant withdraws from the study, information on ulcer outcome at 12 months will be obtained from the participant’s medical files, if a participant consents to this procedure. For participants who do not consent, ulcer outcome will be based on outcome at the moment of withdrawal (last observation carried forward). Ulcer outcome data from participants who die during the study will be based on outcome at the moment of death (last observation carried forward).

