### Sample size {14}

Based on an analysis of RCTs that have recurrent foot ulcers in people with diabetes as outcome, a risk reduction in participants with one or more recurrent foot ulcers up to 75% can be expected from a state-of-the-art multimodal treatment approach [63]. Using a more conservative estimate, we expect a risk reduction of 59% for the enhanced therapy group compared to usual care. This is based on previous studies that show that footwear and at-home foot temperature monitoring interventions combined can achieve such effect sizes [2, 15, 63]. With an expected ulcer recurrence in 37% of the participants in usual care [2, 20], this 59% risk reduction leads to a hypothesized 15% ulcer recurrence rate in the enhanced therapy group. With 15% ulcer recurrence in enhanced therapy and 37% in usual care, *α* = 0.05 (two-sided) and power = 80%, enrolment ratio of 1, power calculations show that 122 participants are required (61 per study group). We expect no dropout or missing data for the intention-to-treat analysis of the clinical outcome based on previous trial experience that clinical outcome can be obtained in each participant [20], which means that a total 122 participants are required for the primary clinical outcome.

For footwear adherence as the primary patient-related outcome measure, we expect 71% (sd 25%) adherence in usual care at 12 months based on findings from previous research [10, 12]. We expect an increase in footwear adherence in the enhanced therapy group to a level of 85% at 12 months, through the effect of indoor footwear provision [12] and structured education. With *α* = 0.05 (two-sided) and power = 80%, enrolment ratio of 1, power calculations show that 100 participants are required (50 per study group). Including a drop-out rate of 20%, this leads to a sample size of 120 participants in total for the primary patient-related outcome.

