For cost-utility as primary health-economic outcome measure, we anticipate a clinically relevant 0.1 gain in QALYs for the enhanced therapy group with group standard deviations for QALYs of 0.15 [64]. We use an estimation of cost difference of €0 per participant between both groups with group standard deviations for costs of €1000 [65, 66]. We allow room here for a more positive outcome in costs, as we predict an average cost saving per participant of €1113.75 for enhanced therapy based on the expected clinical effect of 59% relative reduction in number of ulcers compared with usual care (see Table 1). With a willingness to pay (WTP) of €50,000, a correlation between costs and QALYs (*ρ*) of 0, *α* = 0.05 (two-sided), power = 80%, and a drop-out rate of 20%, this leads to a sample size of 63 participants per study group, or 126 participants in total. Without drop-out, a sample size of (63 × 0.8 =) 51 participants per study group or 102 in total is required.

**Table 1 Tab1:** Average predicted costs per participant

				**Enhanced therapy**		**Usual care**	
**Modality**	**Event/activity**	**Time (hours)**	**Unit costs**	**Expected frequency**	**Expected costs**	**Expected frequency**	**Expected costs**
	Ulcer development [6]	-	€10,000	0.15	€1500	0.37	€3700
	Podiatrist	1	€100	0.50	€50	0.00	€0
Custom-made footwear	Optimization equipment: pressure measurements [36]	-	€50	1.00	€50	0.00	€0
	Shoe technician	1	€100	2.00	€200	0.00	€0
Custom-made indoor footwear	Production and optimization [13]	-	€400	0.95	€380	0.00	€0
Personalized temperature monitoring	Thermometry [38]	-	€75	0.75	€56.25	0.00	€0
Personalized education	Structured education	1	€100	0.50	€50	0.00	€0
	Motivational Interviewing	1	€100	2.00	€200	0.00	€0
	Equipment [49, 57]	-	€100	1.00	€100	0.00	€0
**Total**					€2,586.25		€3,700

Average of predicted additional costs per participant of enhanced therapy versus usual care, based on the expected frequencies as described in the power calculation. For all costs except ulcer development, usual care is used as index. Unit cost estimations are based on previous studies and standard hourly wages of a college educated professional in the Netherlands

With the power calculations showing a requirement of 122 participants for the primary clinical outcome, 120 for the primary patient-related outcome, and 126 for the primary health-economic outcome, a sample size of 126 participants provides adequate power for all three primary outcomes.

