##### Primary study outcomes

For each of the three specified outcomes related to proportion of participants with a recurrent foot ulcer (any ulcer, plantar ulcer, ulcer at high-risk location), effectiveness of the intervention will be assessed using chi-square analysis. Outcome of ulcer recurrence over time will be assessed using log-rank testing and presented as Kaplan–Meier plots censored for death. For adherence to wearing custom-made footwear, Student’s *T*-test for independent samples will be done, provided the data is normally distributed. Cost and utility outcomes will be combined in the economic evaluation to calculate cost (savings) per QALY (gained) per participant (i.e., cost-utility). Incremental cost-utility ratios (ICUR) will be calculated as the ratio between costs and QALY differences between enhanced therapy and usual care. To account for sampling variability, non-parametric bootstrapping stratified for group and participating center category will be done with 5000 replications. Results will be displayed graphically by plotting the bootstrapped differences in costs and QALYs in a cost-utility plane, with the percentage of pairs in each quadrant calculated. Finally, cost-utility acceptability curves (CUAC) for willingness to pay values up to €100,000 will be graphically displayed, with the probability of enhanced therapy being cost-effective over usual care calculated for willingness-to-pay levels of €0,- and €50,000 per QALY gained and €0,- and €20,000 per extra participant without foot ulcer recurrence, respectively.

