#### Methods in analysis to handle protocol non-adherence and any statistical methods to handle missing data {20c}

As the first choice, missing data will be imputed using multiple imputation with a fully conditional specific predictive mean matching model. Baseline characteristics that significantly differ between those with complete and those with missing data will be used as predictors. For sensitivity analysis, other imputation strategies (e.g., with fewer predictors, or single imputation strategies using individual or group means) will be applied as well.

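### Carrying ulcer status forward for withdrawers who refuse medical-file access scores those still ulcer-free at exit as ulcer-free for 12 months, and is not reconciled with the plan's first-choice multiple imputation

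*Protocol article*

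**What the plan says.** All places are in the Protocol article.

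- **Outcome.** Outcomes {12} defines the primary clinical outcome at group level as the share of participants with at least one foot ulcer during the study. Assessments at randomization postpones randomisation for anyone with a current ulcer, so every participant starts without one.
- **Withdrawal.** Plans to promote participant retention and complete follow-up {18b} sets an order. With consent, the 12-month ulcer outcome is taken from medical files. Failing that: "For participants who do not consent, ulcer outcome will be based on outcome at the moment of withdrawal (last observation carried forward").
- **Death.** The same section adds: "Ulcer outcome data from participants who die during the study will be based on outcome at the moment of death".
- **Missing data in general.** Section {20c} states: "As the first choice, missing data will be imputed using multiple imputation". It lists single imputation among the sensitivity analyses and makes no exception for the ulcer outcome.
- **Sample size {14}.** "We expect no dropout or missing data for the intention-to-treat analysis of the clinical outcome". The section explains this by earlier trial experience that the clinical outcome can be obtained for each participant.
- **Analysis.** Primary study outcomes compares proportions by chi-square and, over time, by log-rank test with Kaplan–Meier "plots censored for death".

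**The concern.** For an outcome of the type 'ever had an ulcer', carrying status forward works in one direction only. A participant who ulcerated before leaving is correctly an event. A participant who had not is scored as a full-year success, even after leaving in the second week. Ulcers after exit are lost and none can be wrongly added.

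If this group is equally large in both arms, both observed risks fall and the risk difference shrinks. If it is larger in one arm, that arm looks better than it is.

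The second problem is that two rules cover the same missing value. Carrying forward is a single imputation, a class of method that section {20c} reserves for sensitivity analysis, yet section {18b} makes it the rule for a primary outcome. Two analysts could each follow the protocol and report different primary results. A choice made once data are in hand would look data-driven.

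**Working it through.** **Inputs from the protocol.** "With 15% ulcer recurrence in enhanced therapy and 37% in usual care"; "0.05 (two-sided) and power = 80%, enrolment ratio of 1, power calculations show that 122 participants are required (61 per study group"). Planned total 126, so 63 per group: "a sample size of 126 participants provides adequate power for all three primary outcomes".

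**Inputs assumed.** The protocol gives no rate of unresolved loss (withdrawal plus refusal of file access). Call it *w* and vary it from 0 to 20%. Assume a constant ulcer hazard over 12 months, the same hazard after exit as before, and exit times spread uniformly over the year.

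**Step 1: the protocol's own figure.** Two proportions, pooled variance, no continuity correction:

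n = [1.96·√(2·0.26·0.74) + 0.8416·√(0.37·0.63 + 0.15·0.85)]² / 0.22² = (1.216 + 0.505)² / 0.0484 ≈ 61.2 per group.

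Rounded up this is 62 per group (124 in total), within 2 of the stated 122. Power is 79.9% at 61 per group and 81.1% at 63. The stated size reproduces.

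**Step 2: ulcer status at exit.** Hazard λ = −ln(1 − p). With uniform exit times, the mean probability of an ulcer before exit is m = 1 − p/λ.

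- Usual care: λ = −ln(0.63) = 0.462; m = 1 − 0.37/0.462 = 19.9%.
- Enhanced therapy: λ = −ln(0.85) = 0.1625; m = 1 − 0.15/0.1625 = 7.7%.

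**Step 3: observed risk under carrying forward.** Observed = (1 − w)·p + w·m. For example, at w = 10% usual care gives 0.9·0.37 + 0.1·0.199 = 35.3%, and enhanced therapy gives 0.9·0.15 + 0.1·0.077 = 14.3%.

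Equal loss in both arms, 63 per group:

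| w | Usual care | Enhanced | Difference (points) | Risk ratio | Power |
|---|---|---|---|---|---|
| 0% | 37.0% | 15.0% | 22.0 | 0.405 | 81.1% |
| 5% | 36.1% | 14.6% | 21.5 | 0.405 | 80.0% |
| 10% | 35.3% | 14.3% | 21.0 | 0.404 | 78.7% |
| 20% | 33.6% | 13.5% | 20.0 | 0.403 | 76.1% |

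**Step 4: unequal loss at the design risks.**

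- 0% usual care, 10% enhanced: 37.0% vs 14.3%, difference 22.7 points, risk ratio 0.386.
- 10% usual care, 0% enhanced: 35.3% vs 15.0%, difference 20.3 points, risk ratio 0.425.

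**Step 5: unequal loss with no true effect (37% in both arms).** The spurious difference is the excess loss times (p − m).

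- 10-point excess: 0.10·(0.37 − 0.199) = 1.7 points; two-sided rejection about 5.5%.
- 20-point excess: 0.20·(0.37 − 0.199) = 3.4 points; two-sided rejection about 6.9%.
- Equal loss: rejection stays at 5.0%.

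**The case against.** The strongest reply is that the affected group may be very small. A participant must withdraw, refuse file access and be ulcer-free at exit; carrying forward is only the fallback, and the protocol expects nobody in this group. With equal loss the risk ratio and type I error hardly move, and 5% loss still leaves 80.0% power. With no true effect, a 10-point imbalance moves the result by 0.017 × 63, about one patient. This stands, and it limits the size of the point.

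It can also be said that the specific rule in {18b} overrides the general one in {20c}, after which no ulcer status is left to impute. That is a reasonable reading, but the protocol does not state it. What is missing is a rule of precedence, so this is not a flat contradiction. The reading also leaves in place the method that can only understate risk.

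A reader might infer that the bias favours the intervention, because enhanced therapy adds daily tasks. The documents do not support a direction. Burden is met by adapting, declining or stopping a modality within the trial, and excess loss in usual care would work against the intervention. The ulcer assessors and the investigator doing the primary analysis are also blinded.

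**Conclusion.** The point holds for withdrawals whose 12-month ulcer status cannot be retrieved. For them the rule understates ulcer risk in one direction, and the protocol does not reconcile it with its own first-choice method. The effect is modest: about 1 to 5 points of power for equal loss of 5% to 20%, and 1.7 points of spurious difference per 10 points of imbalance at a common 37% risk. These figures rest on assumed loss rates, a constant hazard and uniform exit times. If those who leave are at higher risk than those who stay, the understatement is larger.

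Two stronger readings are not supported:

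- **Deaths as unknown outcomes.** Ulcer status up to death is known and no ulcer can follow, so counting deaths by status at death already suits the proportion analysis. Censoring deaths in the log-rank test is the usual cause-specific comparison. It is a different analysis and does not contradict the proportion, although the Kaplan–Meier curve need not match the crude proportion.
- **No drop-out for ulcers against 20% for the other two primary outcomes as an inconsistency.** Sample size {14} gives the reason for the ulcer outcome. Adherence and questionnaire data need active participation and cannot be recovered from ulcer records.

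**What to change.** In {18b}, keep medical-file retrieval as the first step. For withdrawals that remain unresolved, and only for these, replace carrying forward in the primary ulcer analysis with one of two options, named in advance:

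1. multiple imputation by arm of ulcer status between exit and month 12, in line with {20c}, with participants who ulcerated before exit kept as events; or
2. a 12-month cumulative ulcer risk per arm that censors at withdrawal and treats death as a competing event (Aalen–Johansen), with the difference in risk as the comparison.

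Both options assume that loss is unrelated to later ulceration given what is known, so keep carrying forward and add a worst-case or tipping-point analysis as sensitivity analyses. State in {18b} and {20c} that this rule governs the ulcer outcome. Deaths can continue to count by ulcer status at death in the proportion analysis; do not impute ulcers after death.

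The cost is a change of wording before analysis, slightly wider intervals and a little more analysis work. No extra visits or participants are needed.

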#### Data management {19}

A complete data management plan has been composed in collaboration with experts in data management of Amsterdam UMC. Data will primarily be collected on paper using case report forms specifically designed for this study and each visit, and saved in an electronic clinical data management platform compliant with all legal and ethical rules (Castor EDC, Amsterdam, the Netherlands), and with restricted range checks on data values. Diaries and questionnaires are completed on paper and saved in the database upon receipt, or completed digitally. Measured data of the Pedar-X and EMED-X systems (Novel GmbH, Munich, Germany) is stored on network drives of Amsterdam UMC, using standardized operating procedures. Raw data from activity monitors (MoveMonitor, McRoberts, the Hague, the Netherlands) and adherence monitors (Orthotimer, Rollerwerk, Balingen, Germany) is stored on the approved servers of the companies and transferred for analysis to Amsterdam UMC network drives using standardized operating procedures. Contractual agreements are in place for the use of measured data from these external parties.

#### Confidentiality {27}

Participants will be coded by the abbreviation of the participating center combined with a 3-digit participant number. All data related to patients will be safely stored in a locked office cabinet or on a password-protected computer file. Only involved researchers will have access to this study information. Participant’s name will only be recorded on the informed consent forms, which will be kept in a locked cabinet with the lead investigator per center, separately from study data. The subject identification log will be kept separate from all other study related datasets, to assure there is no possibility to match study data with identifiable personal data. All study information will be saved for at least 15 years after the study has ended.

#### Plans for collection, laboratory evaluation and storage of biological specimens for genetic or molecular analysis in this trial/future use {33}

Not applicable. No biological specimens for genetic of molecular analysis will be collected for this study.

### Statistical methods

#### Statistical methods for primary and secondary outcomes {20a}

Statistical analysis will be performed after the last follow-up visit of the last participant using SPSS statistical software (IBM Corporation, Armonk, NY). All tests will assess group effects, will be two-sided, and use *P* < 0.05 as significance level. All comparisons between groups are based on both intention-to-treat and final visit end-point analysis.

##### Primary study outcomes

For each of the three specified outcomes related to proportion of participants with a recurrent foot ulcer (any ulcer, plantar ulcer, ulcer at high-risk location), effectiveness of the intervention will be assessed using chi-square analysis. Outcome of ulcer recurrence over time will be assessed using log-rank testing and presented as Kaplan–Meier plots censored for death. For adherence to wearing custom-made footwear, Student’s *T*-test for independent samples will be done, provided the data is normally distributed. Cost and utility outcomes will be combined in the economic evaluation to calculate cost (savings) per QALY (gained) per participant (i.e., cost-utility). Incremental cost-utility ratios (ICUR) will be calculated as the ratio between costs and QALY differences between enhanced therapy and usual care. To account for sampling variability, non-parametric bootstrapping stratified for group and participating center category will be done with 5000 replications. Results will be displayed graphically by plotting the bootstrapped differences in costs and QALYs in a cost-utility plane, with the percentage of pairs in each quadrant calculated. Finally, cost-utility acceptability curves (CUAC) for willingness to pay values up to €100,000 will be graphically displayed, with the probability of enhanced therapy being cost-effective over usual care calculated for willingness-to-pay levels of €0,- and €50,000 per QALY gained and €0,- and €20,000 per extra participant without foot ulcer recurrence, respectively.

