### Outcomes {12}

There are three primary study outcomes in this study, which are:Foot ulcer recurrence during the 12-month follow-upAdherence to wearing custom-made footwearThe cost (savings) per quality-adjusted life year (QALY) gained (i.e., cost-utility)

These represent a clinical, patient-related, and health-economic perspective, respectively. Foot ulcer recurrence is defined as “a break of the skin of the foot that involves as a minimum the epidermis and part of the dermis, in a person who has a history of foot ulceration, irrespective of location and time since the previous foot ulcer” [15], is monitored during the entire study period, and is—on group level—calculated as the proportion of participants with one or more foot ulcers during the study period. Footwear adherence is defined as the percentage of steps taken in prescribed footwear, calculated by combining physical activity and wearing time measurements [44]. It is calculated over 1 week, at baseline and (for outcomes) at 6 and 12 months’ follow-up. Cost-utility is monitored during the entire study period, costs are summed throughout the 12-month period [45], and utility is scored with the EQ-5D-5L questionnaire every 3 months [46].

Secondary study outcomes are as follows: proportion of participants with one or more recurrent foot ulcers on the plantar side of the foot [15]; proportion of participants with one or more recurrent foot ulcers at the predefined personalized high-risk locations [15]; ulcer-free survival days [47]; falls [48]; wearing time of custom-made footwear [49]; in-shoe peak plantar pressure [47]; cumulative plantar tissue stress [44]; footwear wear-and-tear [50]; ulcer risk prediction score [29]; treatment and footwear satisfaction [51]; foot-related self-care [52]; knowledge of foot care [53]; capabilities, opportunities, and motivations (COM-b) score [54]; quality of life (in participants with [55, 56] or without [5] a recurrent foot ulcer during the trial); physical activity [57]; costs [45]; QALYs [46]; and cost-effectiveness [45]. In participants with an ulcer, other secondary outcomes are as follows: time to ulceration [58], ulcer severity [59–61], time to healing [58], and referral time [62]. Definitions for all secondary outcomes are as provided in the reference following each secondary outcome. All secondary outcomes are monitored during the entire study period using assessments and questionnaires during follow-up visits (see Fig. 2).

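### The Kaplan–Meier plot of ulcer recurrence censors deaths, so it slightly overstates actual incidence and shows a different quantity from the primary proportion

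*Protocol article*

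**What the plan says.** The section Outcomes {12} of the protocol article defines the primary clinical outcome at group level as a simple proportion, "calculated as the proportion of participants with one or more foot ulcers during the study period". The section Primary study outcomes, under Statistical methods {20a}, tests that proportion by chi-square. It then adds a log-rank test of recurrence over time, "presented as Kaplan–Meier plots censored for death".

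Deaths are also addressed in the section on retention and complete follow-up {18b}: "Ulcer outcome data from participants who die during the study will be based on outcome at the moment of death". This is done by carrying the last observation forward, so a participant who dies ulcer-free counts as having no ulcer and stays in the denominator. The same section carries forward ulcer status for participants who withdraw and do not consent to use of their medical files. The article does not say how those withdrawals enter the Kaplan–Meier plot.

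The article gives no expected mortality, overall or by arm.

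**The concern.** Kaplan–Meier treats a censored participant as still at risk and exchangeable with those who remain under observation. That suits someone who leaves the study alive, but not someone who has died. With deaths censored, one minus Kaplan–Meier estimates the ulcer risk in a hypothetical population in which nobody dies and those who died would have ulcerated at the survivors' rate. The share of participants who actually develop an ulcer by 12 months is lower wherever ulcer-free deaths occur.

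The primary proportion, with deaths carried forward, targets that actual share. The curve and the proportion are therefore two summaries of one outcome with different estimands. If anyone dies ulcer-free, the 12-month value on the plot will differ from the headline percentage for a reason that the article does not explain. At stake is how the absolute risks and the absolute benefit are read from the figure; the hypothesis test is not at stake.

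**Working it through.** **Inputs from the article (Sample size {14})**
- Risks: "With 15% ulcer recurrence in enhanced therapy and 37% in usual care", a difference of 22 points.
- Design: "0.05 (two-sided) and power = 80%, enrolment ratio of 1".
- Stated requirement: 61 per group, 122 in total. Planned total: 126, or 63 per group.

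**Assumption.** Mortality is not given, so 12-month values of 2%, 5% and 10% are used as a range, first equal between arms and then unequal.

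**Step 1: reproduce the plan's figure.** The pooled-variance formula for two proportions, with mean risk (0.37 + 0.15)/2 = 0.26:

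n = [1.96·√(2·0.26·0.74) + 0.8416·√(0.37·0.63 + 0.15·0.85)]² / 0.22² = (1.216 + 0.505)² / 0.0484 ≈ 61.2 per group.

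This rounds to the stated 61, or to 62 if rounded up. Power is 79.9% at 61 per group and 81.1% at 63. The sample size reproduces and is not in question.

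**Step 2: size of the overstatement.** Take constant hazards over 12 months, h_u for a first ulcer and h_d for death.
- Death hazard: h_d = −ln(1 − d), where d is 12-month mortality.
- Actual ulcer incidence: h_u/(h_u + h_d) · [1 − exp(−(h_u + h_d))]. Set this to 0.37 or 0.15 and solve for h_u. With deaths carried forward and no other loss, this equals the protocol's proportion.
- What the planned plot shows: 1 − exp(−h_u).

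Worked case, d = 10%: h_d = 0.1054.
- Usual care: h_u = 0.4913. Check: 0.4913/0.5967 · (1 − e^−0.5967) = 0.370. The plot shows 1 − e^−0.4913 = 38.8%.
- Enhanced therapy: h_u = 0.1717. Check: 0.1717/0.2771 · (1 − e^−0.2771) = 0.150. The plot shows 15.8%.

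Equal mortality in both arms:

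| Mortality | Usual care, plotted (actual 37%) | Enhanced, plotted (actual 15%) | Plotted gap (actual 22.0) |
|---|---|---|---|
| 2% | 37.4% | 15.2% | 22.2 |
| 5% | 37.9% | 15.4% | 22.5 |
| 10% | 38.8% | 15.8% | 23.0 |

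Unequal mortality (usual care / enhanced):

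| Mortality | Plotted gap (actual 22.0) |
|---|---|
| 5% / 0% | 22.9 |
| 8% / 2% | 23.3 |
| 10% / 3% | 23.6 |
| 0% / 5% | 21.6 |
| 2% / 8% | 21.7 |
| 3% / 10% | 21.7 |

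At equal mortality the excess in usual care is about 2.3 times that in enhanced therapy (at 10%: 1.82/0.78). Under these assumptions the gap therefore narrows only if mortality under enhanced therapy is more than about 2.3 times that in usual care.

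**Step 3: put the size in context.** The standard error of the difference at 63 per group is √[(0.37·0.63 + 0.15·0.85)/63] ≈ 7.6 points. One participant is 1/63 ≈ 1.6 points. The ratio of plotted risks barely moves, from 0.405 to 0.407 at 10% mortality. In simulations with 63 per arm and 4,000 runs, the log-rank test with deaths censored, a subdistribution (Gray-type) test and the chi-square test all had power of about 82% to 83%.

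**The case against.** The strongest reply is that nothing inferential depends on this plot. The primary test is chi-square on a proportion that already keeps ulcer-free deaths in the denominator, so the actual 12-month risk will be reported. The plot is openly labelled as censored for death, and Kaplan–Meier with deaths censored is a natural companion to a cause-specific log-rank test. Follow-up is 12 months, and the exclusion criteria remove people unlikely to survive that long, so deaths should be few. The shift in the gap is at most about one participant per arm in the range examined. All of this stands, and it makes the point minor.

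Three stronger readings are tempting and are not supported:
- **That the plot always exaggerates the benefit.** It does so with equal mortality or more deaths in usual care. With clearly more deaths under enhanced therapy the gap narrows, and the article gives no mortality by arm.
- **That the two rules for deaths contradict each other.** They serve different analyses, a 12-month proportion and a time-to-event display. Both can be carried out; they simply do not estimate the same quantity.
- **That the log-rank test is invalid.** With deaths censored it is a valid comparison of cause-specific ulcer hazards.

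The objection does not remove the core. The article fixes this display explicitly, so it is not a detail left to an unseen analysis plan. A plotted risk that lies above actual incidence is still the wrong one to show beside the primary percentage when a standard alternative is available from the same data.

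**Conclusion.** The point holds as a minor, free improvement. That the plotted risk exceeds actual incidence in any arm with ulcer-free deaths follows from the method and needs no outside figure. The size does rest on assumptions: the planning risks, constant hazards, and a mortality range that the article does not supply. The result is an excess of 0.4 to 1.8 points in usual care and 0.2 to 0.8 points in enhanced therapy. The gap rises by 0.2 to 1.0 points at equal mortality. In the unequal cases tested it rises by 0.9 to 1.6 points with more deaths in usual care, and falls by 0.3 to 0.4 points with more deaths under enhanced therapy. These shifts are small beside a standard error of about 7.6 points. The primary chi-square test, the log-rank test and the sample size stand as planned.

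**What to change.** In the section Primary study outcomes, replace the Kaplan–Meier plots with cumulative incidence (Aalen–Johansen) curves of first ulcer, treating death before an ulcer as a competing event. Report the 12-month cumulative incidence per arm with a confidence interval, and the number of deaths per arm. Keep the log-rank test and label it as a comparison of cause-specific ulcer hazards.

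The curve and the primary proportion then agree as far as deaths are concerned. They may still differ because of participants who withdraw without consent to file review: the proportion carries their status forward, whereas a time-to-event curve would normally censor them. State how they enter the curve, and note this under the figure.

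The cost is a sentence or two in the analysis section and a short script, possibly outside SPSS. No new data are needed, because the planned plot already requires the ulcer and death dates.
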